**Discussion:**

A total of 259 RYGB female patients has been enrolled in the “WELL-GBP”-trial, of which 156 women have been randomized to receive the intervention and 103 women to control group. The trial is conducted within a Swedish health care setting where female RYGB patients from diverse geographical areas are represented. Our results may, therefore, be representative for female RYGB patients in the country as a whole. If the intervention is effective, implementation within the Swedish health care system is possible within the near future.

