The third session focused on social relations, including family, friends and colleagues. The participants were given the opportunity to reflect on and to role play different scenarios they often experienced themselves. For example, people around them tried to get them to eat foods that are unsuitable after RYGB, gave unhelpful comments or criticisms, or they found themselves at a restaurant with big portions and/or lack of suitable menu options. As a homework exercise each participant wrote a letter to herself to be sent back to her after six months, containing overall goals, mindset and strategies and at least one “lesson learned” from the group sessions.

The fourth session dealt with intimate relations and sexuality. The participants were asked to reflect on and to discuss possible expectations, from themselves and from their partners, as well issues related to lack of a partner, which might arise after surgery. In addition to this, this session also included (fictional) letters. These might have to do with experiencing or not experiencing sexual desire, feelings about one’s own body following major weight loss, and to deal with desired or unwanted sexual attention from others.

During the four sessions, the majority of participants expressed a desire to have more group meetings approximately one year after the surgery, since they felt they wanted to discuss problems and strategies when they had recovered and started to get into their new habits post-surgery. Therefore, a booster session was added and was held approximately one year after surgery. The booster session was a compilation of the four previous sessions. The participants were asked to reflect on the previous topics: PA, eating behavior, social relations and intimate relations and sexuality for approximately ten minutes per topic. Lastly, participants were encouraged to share the experience of receiving the letter six months after they had written it to themselves and to further reflect on experienced problems and possible resolutions after surgery. To the best of our knowledge, none of the participants included in the “WELL-RYGB” Intervention study have suffered any adverse effects so far.

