### Statistical analyses

The statistical analyses will focus on differences between the intervention and the control group from pre-surgery assessment to follow-up assessments at 24 months after RYGB. The women’s changes in weight will be taken into account in the analysis by stratification or adjustment. Primary analysis will be intention to treat analysis, including women who attended at least one session (*n* = 103). We will also conduct per protocol analysis including the women who have attended all four sessions (*n* = 33). We will also perform sensitivity analysis in order to detect any possible dose-response effects such as if the main outcomes will differ depending on if a woman have attended one, two three or all four sessions. Furthermore, individual factors, e.g. patient beliefs about causality of obesity, and contextual factors, e.g. variations in implementation of the intervention between centers for bariatric surgery, might moderate the effect of the intervention on health outcomes. These issues will be analyzed by mixed linear regression models or generalized estimation equations (GEE) to analyze repeated measurements over time. [41].

For the assessments of the baseline characteristics for the intervention and control group presented in this protocol, the analysis have been separated into women randomized to intervention group and women randomized to control. X^2^-tests were performed for categorical variables and t-tests for continuous variables, and because the majority of the continuous variables were not linear distributed, the Kruskal-Wallis test was used.

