To reduce the problems associated with drop-out, a larger proportion (60%) of the participants were randomized to intervention. Unfortunately, 34% (*n* = 53) of the women in the intervention group did not attend any of the intervention sessions, even though they agreed to participate when invited and had completed the baseline assessments. This may have a negative effect on the upcoming results, but in accordance with the power calculations (see above), a minimum of 95 participants was needed to attain a statistical power of at least 0.80. In this trial 103 women (66%) in the intervention group completed the baseline assessments and attended at least one of the intervention session. Even so, the results may not be representative to the general Swedish women who undergo RYGB surgery.

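### The per-protocol and dose-response analyses are non-randomised contrasts, confounded by who attends, and the plan states no method to deal with that

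*Protocol article*

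**What the plan says.** All in the protocol article, section Statistical analyses unless stated otherwise.

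- General comparison: "The statistical analyses will focus on differences between the intervention and the control group from pre-surgery assessment to follow-up assessments at 24 months after RYGB".
- Primary set: "Primary analysis will be intention to treat analysis, including women who attended at least one session", given as 103 women.
- Per-protocol set: "We will also conduct per protocol analysis including the women who have attended all four sessions", given as 33 women. No matching restriction of the control arm is described.
- Dose-response: a sensitivity analysis is to look at "if the main outcomes will differ depending on if a woman have attended one, two three or all four sessions". No control comparator is named here.
- Covariates: "The women’s changes in weight will be taken into account in the analysis by stratification or adjustment". Nothing that predicts attendance is named.
- Arm sizes (Abstract, Discussion): "156 women have been randomized to receive the intervention and 103 women to control group".
- Non-attendance (Discussion): 34%, or 53, "of the women in the intervention group did not attend any of the intervention sessions, even though they agreed to participate when invited".
- Booster (Intervention description): after participants asked for more meetings, "a booster session was added and was held approximately one year after surgery". It went over all four topics again and fell before the 24-month endpoint. Neither the per-protocol set nor the session count mentions it.

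**The concern.** Randomisation makes the 156 and the 103 comparable. It does not make the 33 who came to every session comparable with the 103, because the control arm contains an unidentified share of women who would also have come to everything and a larger share who would not. Any difference in motivation, health or life circumstances between full attenders and the rest goes straight into the per-protocol estimate.

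The by-session analysis has the same weakness inside the intervention arm. Women who come once and women who come four times chose to do so, and a gradient in who they are cannot be told apart from a gradient in what the sessions did.

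The one adjustment named, change in weight, is measured after randomisation and does not address selection into attendance.

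A per-protocol analysis often does little harm because a full intention-to-treat result stands beside it. Here the primary set is itself limited to attenders, so as written no efficacy analysis compares all 156 with all 103. A favourable result among full attenders would have no randomised result to be checked against.

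**Working it through.** **Inputs from the document.** Randomised: 156 and 103. Attended at least one session: 103. Attended all four: 33. Attended none: 53. Expected drop-out: 20%. (Other sections print 153 or 163 for the intervention arm. I use 156 because 156 + 103 = 259, the stated total.)

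**The plan's own fractions.** 103/156 = 66.0% and 53/156 = 34.0%, as printed. The per-protocol set is 33/156 = 21.2% of the arm and 33/103 = 32.0% of the attenders.

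**Inputs assumed.** The article gives no data by attendance. I therefore suppose a normally distributed tendency to attend, with the 33 being the top p = 0.2115 of it, and a correlation r between that tendency and the outcome. I take r from 0.1 to 0.3, unadjusted for baseline. The true effect is set to zero.

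**Spurious per-protocol effect.** The mean tendency among the top fraction p is φ(c)/p, where c is the upper p point of the standard normal. With c = 0.801 this is 1.368. Controls are unselected, with mean 0, so bias = 1.368 × r SD.

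**False-positive rate.** After 20% loss in each group, about 26 and 82 women remain. SE = √(1/26 + 1/82) = 0.225 SD. The two-sided 5% rejection rate is Φ(bias/SE − 1.96) + Φ(−bias/SE − 1.96).

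| r | bias (SD) | bias/SE | rejection rate |
|---|---|---|---|
| 0.1 | 0.14 | 0.61 | 9% |
| 0.2 | 0.27 | 1.22 | 23% |
| 0.3 | 0.41 | 1.82 | 45% |

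Simulation gives much the same (9%, 22% to 24%, 44% to 45%).

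**A second model, as a check.** Let full attenders differ from the other intervention women by g SD. Bias = g × (1 − 0.2115). For g = 0.1, 0.2, 0.3 and 0.5 this is 0.08, 0.16, 0.24 and 0.39 SD. With 33 against 103 and no loss, the rejection rates are 6.8%, 12.4%, 21.9% and 50.4%.

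**By-session contrast.** Under the first model the 103 attenders have mean tendency 0.555. The 70 who came one to three times then have (103 × 0.555 − 33 × 1.368)/70 = 0.171. With zero effect, full attenders exceed them by (1.368 − 0.171) × r = 1.20 × r SD, which would look like a dose-response.

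**Power of the per-protocol set.** With 26 against 82, power at d = 0.50 is 0.60, and the smallest d detectable with 80% power is 0.64.

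**Cost of the alternative.** A complier average causal effect for attending at least one session is the intention-to-treat effect divided by 0.660, so its SE is 1/0.660 = 1.5 times as large. With about 125 and 82 followed, the intention-to-treat SE is 0.142 SD and the complier SE about 0.142/0.660 = 0.215 SD. That is close to the 0.225 of the 33-woman contrast, although the two target different effects.

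**The case against.** Five points can be made for the plan.

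1. *These are supplementary analyses with exploratory wording, and an unseen analysis plan may say more.* This holds, and it limits the weight of the point. But the article does fix the set of 33 and the dose-response reading, and the primary set offers no randomised contrast to fall back on.

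2. *A reader might infer that these analyses mainly measure who attends rather than what attending does.* The document does not support that. It gives no data by attendance, so both r and its sign are assumed. If women with more problems attended more, the bias would run against the intervention. Even at r = 0.3 the bias of 0.41 SD is below the planned effect (printed as 50, read as 0.50). It reaches 0.50 only at r = 0.50/1.368 = 0.37, or at a gap of about 0.63 SD in the second model.

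3. *A reader might infer that both analyses use all controls as comparator.* Only the per-protocol analysis does, and by implication. The dose-response sentence reads as a comparison among attenders. That comparison is still not randomised.

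4. *The comparison runs from the pre-surgery assessment.* If selection works partly through baseline health, allowing for baseline would shrink the bias, so the figures above lean high. Motivation and later circumstances would remain.

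5. *The booster was added later, and the randomised intervention was four sessions.* Defining the per-protocol set by those four is defensible. Leaving the booster out is not what causes the selection bias. It only means that the session count is an incomplete record of what was received before 24 months.

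**Conclusion.** The point holds in this form: the per-protocol contrast (33 of 156, by implication against all controls) and the by-session contrast are non-randomised and confounded by who attends, and no handling of selection is stated. With no true effect and an assumed correlation of 0.1 to 0.3 between attendance and outcome, the per-protocol contrast carries a spurious effect of about 0.14 to 0.41 SD and a false-positive rate of about 9% to 45%. These figures rest on a normal tendency-to-attend model, a positive sign, no baseline adjustment and equal 20% loss. They show the possible size of the problem and do not estimate the bias in this trial. Because the analyses are secondary, this is something that should be changed. The restriction of the primary set to attenders is a separate and graver matter, and this point would remain after that one was put right.

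**What to change.** - Estimate the effect of attending as a complier average causal effect of attending at least one session, with randomised arm as instrument. Keep all 259 women as randomised, with missing 24-month data handled under a stated assumption. Adjust for baseline SF-36 and randomisation stratum (the three Stockholm-area hospitals together, Uppsala, Örebro). As described, controls received usual follow-up only, so non-compliance is one-sided.
- State the exclusion restriction: allocation has no effect on women who attend nothing. State also that this estimate concerns attending at least one session. It does not give the effect of all four sessions, nor a dose relation.
- Report the 33-woman and by-session results as descriptive and non-randomised, drop the dose-response interpretation and the sensitivity label, and show booster attendance alongside.

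Cost: a change of wording and one two-stage model, using attendance records that the trial must already hold to have counted 103 and 33. The downside is a standard error about 1.5 times that of the intention-to-treat analysis, and no formal answer to whether more sessions do more.

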Role Emotional (RE)	77.2 (28.0)	77.3 (28.5)	0.912
Mental Health (MH)	64.9 (19.5)	64.9 (21.4)	0.770
Physical component summary score (PCS)	41.6 (9.5)	42.9 (9.6)	0.205
Mental component summary score (MCS)	45.8 (11.0)	45.9 (11.3)	0.848
Prevalence of risk of depression (MCS score ≤ 42), % (n)	35.1 (54)	30.7 (31)	0.469

^a^One participant in the intervention group and one participant in the control group did not answer the SF-36 questionnaire

Baseline measurement of the women’s levels of PA, sedentary behavior and wear time are presented in Table 4. The women in the intervention group wore the accelerometer for a mean of 6.6 ± 1.1 days, spent 28.8 ± 17.5 min/day in MVPA and 465.1 ± 98.0 min/day was spent sedentary. For the control group, the women wore the accelerometer for a mean of 6.9 ± 1.4 days, spent 28.8 ± 22.4 min/day in MVPA and were sedentary for 447.0 ± 104.2 min/day.

**Table 4 Tab4:** Baseline total and intensity-specific levels of accelerometer-measured physical activity (PA) and sedentary behavior (SB) of women undergoing RYGB Surgery

Characteristic	Intervention (*n* = 97^a^) Mean (SD)	Control (*n* = 58^a^) Mean (SD)	*p*-value
Wear time: nr of days (≥10 h/day)	6.6 (1.1)	6.9 (1.4)	0.169
Wear time: hours/day	14.4 (1.2)	14.3 (1.1)	0.369
Total PA (cpm)	576.6 (179.3)	621.2 (230.1)	0.342
Moderate to vigorous PA (min/day)	28.8 (17.4)	28.8 (22.4)	0.579
Light PA (min/day)	369.4 (88.1)	380.2 (78.1)	0.518
SB (min/day)	465.1 (98.0)	447.0 (104.1)	0.399

^a^59 participants in the intervention group and 45 participants in the control group declined to wear an accelerometer or the timing for wearing an accelerometer were too close to their surgery date

## Discussion

The ongoing RCT with a dissonance-based intervention, “WELL-GBP”, targeting female RYGB patients in a health care setting, aims to improve HRQoL and health-related behaviors after RYGB. The intervention is manual-based, free of charge, delivered in health care settings and could be delivered by health-care personnel such as nurses, dietitians, physiotherapists or counsellors, after some practice. We are not aware of any previous randomized controlled trial that has investigated the effects of a similar intervention on HRQoL and following RYGB.

Previous studies using dissonance-based interventions have had positive results on health outcomes and showed greater effect sizes compared to non-dissonance-based interventions or no intervention, regarding disordered eating, body dissatisfaction [24–26], and also increased PA at post-test, but not at 1–2 year follow-up [25, 26]. This trial uses a modified version of Stice’s dissonance-based prevention model and has been adapted to RYGB patients.

The women participating in this trial could be representative of women who undergo RYGB surgery in Sweden, as they are from different geographical areas and are similar in age and BMI at the time of surgery to other RYGB patients in Sweden [42]. They are also comparable in this respect to other bariatric patients from other parts of the world, although they tend to be slightly older and have a higher BMI [43]. A previous study comparing levels of PA pre-bariatric surgery measured by an accelerometer in Swedish women have similar characteristics in the different PA levels as the women in the “WELL-GBP” trial [44]. HRQoL in our sample was similar, although somewhat higher, than the general Swedish bariatric surgery patients [45]. HRQoL, especially PCS score, improves after bariatric surgery and is related to weight loss, gender and age, with lower PCS and MCS scores in women than men, and lower PCS but higher MCS with increased age [45].

The current “WELL-GBP” trial only includes Swedish-speaking women, as resources such as an interpreter at the group sessions were not feasible. This may affect the external validity as the future results will not be representative of women who live in Sweden but don’t master the Swedish language. Also, because this current trial only includes women, any possible intervention effect on men who undergo RYGB will not be possible to predict.

To reduce the problems associated with drop-out, a larger proportion (60%) of the participants were randomized to intervention. Unfortunately, 34% (*n* = 53) of the women in the intervention group did not attend any of the intervention sessions, even though they agreed to participate when invited and had completed the baseline assessments. This may have a negative effect on the upcoming results, but in accordance with the power calculations (see above), a minimum of 95 participants was needed to attain a statistical power of at least 0.80. In this trial 103 women (66%) in the intervention group completed the baseline assessments and attended at least one of the intervention session. Even so, the results may not be representative to the general Swedish women who undergo RYGB surgery.

### Conclusions

The “WELL-GBP” trial is conducted within a Swedish health care setting where female RYGB patients from diverse geographical areas are represented. Our results may, therefore, be representative for female RYGB patients in the country as a whole. If the intervention is effective, implementation within the Swedish health care system is possible within the near future.

## Abbreviations

BMI: Body mass index
HRQoL: Health related quality of life
KI: Karolinska Institutet
MVPA: Moderate to vigorous physical activity
PA: Physical activity
RYGB: Roux-en-Y gastric bypass
WELL-GBP: Wellbeing after gastric bypass
